## Abstract

**Background:**

Chronic Obstructive Pulmonary Disease (COPD) is a growing worldwide problem that imposes a great burden on the daily life of patients. Since there is no cure, the goal of treating COPD is to maintain or improve quality of life. We have developed a new tool, the Assessment of Burden of COPD (ABC) tool, to assess and visualize the integrated health status of patients with COPD, and to provide patients and healthcare providers with a treatment algorithm. This tool may be used during consultations to monitor the burden of COPD and to adjust treatment if necessary. The aim of the current study is to analyse the effectiveness of the ABC tool compared with usual care on health related quality of life among COPD patients over a period of 18 months.

**Methods/Design:**

A cluster randomised controlled trial will be conducted in COPD patients in both primary and secondary care throughout the Netherlands. An intervention group, receiving care based on the ABC tool, will be compared with a control group receiving usual care. The primary outcome will be the change in score on a disease-specific-quality-of-life questionnaire, the Saint George Respiratory Questionnaire. Secondary outcomes will be a different questionnaire (the COPD Assessment Test), lung function and number of exacerbations. During the 18 months follow-up, seven measurements will be conducted, including a baseline and final measurement. Patients will receive questionnaires to be completed at home. Additional data, such as number of exacerbations, will be recorded by the patients’ healthcare providers. A total of 360 patients will be recruited by 40 general practitioners and 20 pulmonologists. Additionally, a process evaluation will be performed among patients and healthcare providers.

**Discussion:**

The new ABC tool complies with the 2014 Global Initiative for Chronic Obstructive Lung Disease guidelines, which describe the necessity to classify patients on both their airway obstruction and a comprehensive symptom assessment. It has been developed to classify patients, but also to provide visual insight into the burden of COPD and to provide treatment advice.

**Trial registration:**

Netherlands Trial Register, NTR3788.

## Background

The prevalence of Chronic Obstructive Pulmonary Disease (COPD) is increasing globally due to an aging population and continued exposure to risk factors [1]. COPD has a major impact on the lives of patients’. The prevalence of COPD is expected to increase, and is projected to be the fourth leading cause of death and the seventh leading cause of disability-adjusted life years (DALYs) lost worldwide by 2030 [2,3].

Since there is no cure for the disease, the goal of COPD treatment is to maintain or improve patients’ quality of life. As such, the care of patients with COPD is currently shifting towards a more patient-centred model. More attention is paid to the impact of the disease on the patient’s life [1]. It is therefore necessary to focus on more than just airway obstruction, as measured by the forced expiratory volume in one second (FEV1), which has a poor correlation with many patient reported outcomes in COPD [4]. Health status measurements have been propagated as an important part of managing COPD, both in primary and secondary care [5]. Previous studies showed that a poor health status is a predictor for hospitalization and mortality [6-8].

Health status questionnaires can also be used to determine the burden of COPD as experienced by patients. However, current health status questionnaires do not fully cover patients’ experienced burden of disease [9]. Hence, we developed a new tool, the Assessment of Burden of COPD (ABC) tool, which consists of three elements. The first element is the ABC scale, a 14-item questionnaire that measures five different domains of the burden of disease as experienced by the patient: symptoms, functional state, mental state, emotional state, and fatigue. The second element comprises a number of additional indicators: smoking status, exacerbation history, dyspnoea, body mass index (BMI), lung function and physical activity. When combined with the ABC scale an overall assessment of a patient’s integrated health status is obtained. The third element is a computer program used to visualize the scores on all items into green, orange and red balloons and link treatment advice to these balloons (see Figure 1) [9].

**Figure 1 F1:**
[figure not shown]
Visualization of the dimensions influencing integrated health status (Assessment of Burden of COPD tool), changed after treatment.

The purpose of the ABC tool is to assess the experienced burden of disease and to provide both patient and healthcare provider with a visual overview of the individual patient’s burden of COPD. The tool is designed to facilitate shared decision making, in which patients and healthcare providers are both responsible for the focus of treatment , selecting the corresponding treatment options, formulating a personal goal and make a tailored treatment plan [10]. Patients need to be encouraged to take the lead in their own treatment, and the ABC tool aims to facilitate in this process. It can be used during consultations to monitor the patient’s integrated health status, including the experienced burden of COPD, and to treat the patient accordingly.

The development of the tool has been described elsewhere [9].

The reliability, validity and responsiveness of the ABC scale, the first element and core component of the ABC tool, still needs to be assessed. The scale is based mainly on the Clinical COPD Questionnaire (CCQ) [11], so we assume that it is a valid and reliable instrument. However, to be thorough we will analyse the internal consistency and test-retest reliability. Furthermore, we will analyse the convergent validity, divergent validity, known-group differences and responsiveness.

Since the effectiveness of the ABC tool has not yet been tested, we will conduct a cluster randomised controlled trial (RCT). The trial will take place in both primary and secondary care settings, to include patients with varying disease severity. We aim to evaluate the effectiveness by answering the following research question:

In COPD patients, varying in disease severity, does application of the ABC-tool increases the percentage of patients with a clinically relevant improvement on the Saint George Respiratory Questionnaire (SGRQ) [12], between baseline and 18 months follow-up, as compared with usual care?

## Methods/Design

### Study design

The study is a two-armed cluster RCT that compares an intervention group, using the ABC tool with a control group receiving usual care. The duration of follow-up period is 18 months. During this period there are seven measurements, including a baseline and final measurement. The flow of the study is presented in Figure 2.

**Figure 2 F2:**
[figure not shown]
Flow of the study.

This study has been approved by the Medical Ethics Committee of the Atrium-Orbis-Zuyd Hospital in the Netherlands.

### Selection, recruitment and randomisation

This study will take place in general practices and hospitals throughout the Netherlands. The researchers will contact general practitioners (GPs) and pulmonologists using a GP network (CAHAG; COPD and Asthma GP Advice Group) and the pulmonologists association (NVALT; Dutch Association of Physicians for Lung Diseases and Tuberculosis). To avoid contamination of care (i.e. patients from the control group receiving the intervention because they are treated by the same caregiver), it is vital that the randomisation between the groups takes place at caregiver-level and not at patient-level. Therefore, healthcare providers will be randomly assigned to intervention or control group in a 1:1 ratio with the help of a computer program designed by the Maastricht University Centre for Data and Information Management (MEMIC). Randomisation will be stratified by type of caregiver (GP or pulmonologist) and variable blocks of two, four or six will be used to make sure there are an equal number of caregivers from primary and secondary care in the intervention and control group. The researcher will enter the names of the healthcare providers into the computer program, which will then randomly allocate them to either the intervention or control group.

Participating healthcare providers will be asked to invite patients from their listed patient databases to participate in the trial. Patients that meet the inclusion criteria and exclusion criteria (see next paragraph) will be sent an information letter including an informed consent form. Healthcare providers will also directly invite patients to participate if they see them during consultations. If the patient agrees to participate in the study, an appointment will be made with the healthcare provider to discuss further details of the trial, recheck whether the patient is eligible for the study and sign the informed consent form.

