### Intervention group

The actual intervention will be the use of the ABC tool by patients and healthcare providers during routine consultations. Patients will fill out the ABC scale, which measures the patient’s experienced burden of COPD, in the waiting room (without supervision) [9]. The healthcare provider will then enter the results of the ABC scale into a computer program and add the results of additional items (i.e. smoking status, exacerbation history, dyspnoea, body mass index (BMI), lung function and physical activity). These items and the ABC scale together will show the integrated health status of the patient, illustrated by a visual representation with coloured balloons. The balloons represent all of the patient’s health status items, including the different domains of the ABC scale (see Figure 1). A high, green balloon means that the patient scores well on a particular item/domain; an orange balloon means an intermediate score; and a low, red balloon means that the patients scores poorly on that item/domain. Patients and healthcare providers will be prompted to discuss the balloons together, according to the principles of shared decision making (SDM) [13], and will be advised to work on the items represented by the red and orange balloons. These represent the items with possible room for improvement if the right treatment is provided. Each balloon can be clicked on, showing a pop-up with treatment advice.

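### As the article describes recruitment, allocated providers who cannot be blinded invite, recheck and consent their own patients, with no stated concealment or rule on whom to approach, so the arms could be recruited differently in either direction

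*Protocol article*

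**What the plan says.** Everything on recruitment is in the protocol article, Selection, recruitment and randomisation. To avoid contamination, "it is vital that the randomisation between the groups takes place at caregiver-level and not at patient-level". On the mechanism: "The researcher will enter the names of the healthcare providers into the computer program, which will then randomly allocate them" to an arm, stratified by type of caregiver.

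The next paragraph gives two routes into the trial:

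- **List route.** "Participating healthcare providers will be asked to invite patients from their listed patient databases to participate in the trial". Patients who meet the criteria are sent an information letter with a consent form.
- **Consultation route.** "Healthcare providers will also directly invite patients to participate if they see them during consultations".

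For patients who agree, "an appointment will be made with the healthcare provider to discuss further details of the trial, recheck whether the patient is eligible for the study". Consent is signed at that same appointment. The provider therefore invites, confirms eligibility and takes consent.

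The section Intervention group shows that the provider runs the intervention: "The healthcare provider will then enter the results of the ABC scale into a computer program". The section Control group says that the tool is supplied only to the intervention arm and that control providers get no instruction from the research team. The primary outcome is a fall of at least 4 points on the patient-completed SGRQ from baseline to 18 months.

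**The concern.** Randomising clusters balances the providers. It balances the patients only if they are identified before the arm is known, or by a process that the arm cannot influence. Here one person, who cannot be blind once allocated, controls invitation, the eligibility recheck and consent. Nothing in the article says that this person is unaware of the arm while recruiting, or that the patients approached are fixed in advance.

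What patients agree to also differs by arm. The Measurements section gives at least four provider visits over 18 months in the intervention arm, against visits at baseline and 18 months in the control arm. Consent could therefore differ without any deliberate choice by the provider.

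The outcome is sensitive to who enters. A patient with a baseline SGRQ below 4 cannot respond at all, and motivation plausibly affects both consent and self-reported change. If the arms differ in such traits, the difference in responder proportions mixes the effect of the tool with the make-up of the arms. Adjusting for measured baseline values would remove only part of this, and a larger sample would remove none of it.

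**Working it through.** **Text, side by side.** Three conditions together create the risk.

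1. Recruiters may know the arm. The article randomises providers and then describes recruitment by participating providers. It mentions no withholding of the allocation, and the tool cannot be hidden from the person who operates it.
2. Recruiters have discretion. The letter route limits it, since letters go to patients who meet criteria common to both arms. The consultation route has no sampling rule, and the recheck and consent rest with the provider.
3. The outcome depends on patient traits. It is a self-reported change with a threshold.

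**The plan's own sample size, reproduced.** Inputs from Sample size calculation: 50% against 30%, two-sided 5%, 80% power, 5 patients per GP and 8 per pulmonologist, ICC 0.05, and factors 1.38, 1.33 and 1.10.

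- Per arm, unpooled formula: (0.50×0.50 + 0.30×0.70) × (1.960 + 0.842)² / 0.20² = 90.3. The plan says 90.
- Mean cluster size: (20×5 + 10×8)/30 = 6. Design effect: (1 + 5×0.05) × 1.10 = 1.375. The plan says 1.38.
- Inflation: 1.38 × 1.33 × 1.10 = 2.019, and 180 × 2.019 = 363. The plan says 360.

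The sample size is sound and is not in question. Turning the inflation around gives the effective size per arm: 180/2.019 = 89.

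**Illustration 1: shift towards the intervention, no true effect.** Assume both arms would respond at the plan's control rate of 30%, and that differential recruitment alone adds a shift s to the intervention arm.

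- SE = √(2×0.30×0.70/89) = 0.0687.
- Rejection probability = Φ(s/SE − 1.96) + Φ(−s/SE − 1.96).
- s = 0.04: s/SE = 0.582, giving Φ(−1.378) + Φ(−2.542) = 0.090.
- s = 0.06: s/SE = 0.873, giving Φ(−1.087) + Φ(−2.833) = 0.141.

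Shifts of this size arise, for example, if the arms differ by 20 points in the share of a subgroup whose responder rate differs from other patients' by 20 points (0.20×0.20 = 0.04) or by 30 points (0.20×0.30 = 0.06). None of these subgroup figures is in the documents.

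**Illustration 2: shift against the intervention, planned effect true.** Assume that recruitment lowers the intervention rate from 50% to 45%, with control at 30%. Use the pooled standard error for the critical value and the unpooled one for the spread.

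- No shift: (0.20 − 1.96×0.0734)/0.0718 = 0.78, so power is 0.78 (nominally 80%).
- 5-point shift: (0.15 − 1.96×0.0725)/0.0716 = 0.11, so power is 0.54.

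**The case against.** The strongest counter-argument is that the sequence is inferred. The article never states when a provider learns the arm, or that patients are recruited after disclosure. The section heading puts selection and recruitment before randomisation, and the flow figure, which might settle the order, is not shown. This stands as a limit on confidence. It does not remove the point, because the text as written allocates providers and then sends them to recruit, with no safeguard stated.

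The letter route is also a real restraint. Read plainly, letters go to the patients who meet the criteria, not to a chosen few, and the criteria are the same in both arms and largely objective. That narrows the concern to the consultation route and provider-led consent. The article does not say how many patients will enter through consultations.

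A reader might also infer that each provider picks a handful from a much longer list. The article gives no list size. Its 5 per GP and 8 per pulmonologist are average estimates of the patients available, not quotas drawn from a larger pool.

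Finally, a condensed article can leave screening logs and the handling of allocation to the full protocol. That is fair for the logs. It does not cover opportunistic invitation and provider-led consent, which the article states as the procedure.

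**Conclusion.** The concern holds as a risk built into the described procedure, with medium confidence because the order of allocation and recruitment is inferred. The sponsor should deal with it.

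Its size cannot be derived from the documents. Under the assumed shifts, the two-sided error rises from 5% to about 9% at 4 points and about 14% at 6 points, while a 5-point shift the other way cuts power from about 80% to about 54%. These results rest on 89 effective patients per arm, a control rate of 30%, a simple two-proportion test and no covariate adjustment.

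A reader might go further and infer that intervention providers will favour patients likely to improve, that control providers have no comparable motive, and that the trial is therefore biased towards the tool. The documents do not support this. They say nothing about motives, and providers using a tool centred on burden might instead enrol sicker patients who are less able to improve. Nor do they show that differential recruitment has occurred.

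**What to change.** - Before a provider's allocation is disclosed, have the provider generate and lock a list of candidate patients from the stable criteria: spirometry-confirmed COPD, age and language.
- Invite from that list by the same rule in both arms: either everyone, or in random order until the target is reached.
- Restrict consultation invitations to patients on the locked list.
- Recheck time-varying criteria at enrolment, in particular an exacerbation in the previous six weeks. A list of fully eligible patients locked in advance would go out of date.
- Report eligible, invited and consenting numbers by arm. This can still be done if recruitment has begun, and it would help to show whether recruitment differed.

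If allocation is already withheld until patients are listed, stating so, with the rule for inviting them, would settle most of the point.

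**Cost:** slightly later release of each allocation, modest list-preparation work for each of the 60 providers, somewhat slower recruitment, and the loss of patients newly diagnosed after the list is locked. The sample size does not change.

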### Inclusion and exclusion criteria

The inclusion criteria will be: a confirmed diagnosis of COPD (post-bronchodilator FEV1/Forced Vital Capacity < 0.7) by spirometer, age 40 years or above, and the ability to understand and read the Dutch language. The exclusion criteria will be: an exacerbation less than six weeks ago, hard-drug addiction, life-threatening co-morbid conditions, and current pregnancy. Exacerbations are defined as an acute event characterized by worsening of a patient’s respiratory symptoms beyond normal day-to-day variation that necessitates prednisolone and/or hospital admissions for COPD.

### Intervention group

The actual intervention will be the use of the ABC tool by patients and healthcare providers during routine consultations. Patients will fill out the ABC scale, which measures the patient’s experienced burden of COPD, in the waiting room (without supervision) [9]. The healthcare provider will then enter the results of the ABC scale into a computer program and add the results of additional items (i.e. smoking status, exacerbation history, dyspnoea, body mass index (BMI), lung function and physical activity). These items and the ABC scale together will show the integrated health status of the patient, illustrated by a visual representation with coloured balloons. The balloons represent all of the patient’s health status items, including the different domains of the ABC scale (see Figure 1). A high, green balloon means that the patient scores well on a particular item/domain; an orange balloon means an intermediate score; and a low, red balloon means that the patients scores poorly on that item/domain. Patients and healthcare providers will be prompted to discuss the balloons together, according to the principles of shared decision making (SDM) [13], and will be advised to work on the items represented by the red and orange balloons. These represent the items with possible room for improvement if the right treatment is provided. Each balloon can be clicked on, showing a pop-up with treatment advice.

The algorithm behind the ABC tool was developed based on a previous treatment algorithm attached to the CCQ [14], and optimized for this study according to national and international guidelines [15-17]. The cut-off points are based on the current Dutch COPD Healthcare Standard guidelines [18], and experts’ experiences. The level of the balloon was determined by using a continuous scale to grade the displayed value. The treatment recommendations were written by pulmonologists and GPs based on the current national COPD guidelines. Two versions of the algorithm were written, one for the use in primary care, based on the standard of the Dutch College of General Practitioners [15] and the other for the use in secondary care, based on the NVALT guidelines [16]. The treatment advice was written during a number of meetings and groups discussions, and the algorithm was tested extensively by healthcare providers with different backgrounds throughout the Netherlands. Examples of the treatment advice are provided in Additional file 1.According to the principles of shared decision making, patients and healthcare providers will be advised to discuss the possible treatment options within the patient’s possibilities. One or more pieces of advice can be selected and will automatically and electronically be placed in the patient’s written treatment plan. During the consultation, healthcare providers should guide patients in setting a personalized treatment goal. This personal goal should be written down as an achievable goal, in the patient’s own words. The treatment plan aims to achieve the personal goal. At each follow-up moment, the intervention group will complete the ABC scale and use the ABC tool. The tool will show both the current balloons and the balloons from the previous consultation, displayed in grey (Figure 1). The tool can be used to monitor a patient’s integrated health status over time and adjust the treatment as necessary.

### Control group

The ABC scale and tool (including its software) will only be provided in the intervention group. The patients in the control group will receive care as usual and their healthcare providers will not be instructed by the research team.

### Measurements

#### ***Intervention group***

Patients in the intervention group will receive individualized treatment guided by their integrated health status, as measured predominantly by the ABC scale. Patients will visit their healthcare providers at least four times during the 18 months follow-up. During these consultations, healthcare providers will record lung function, number of exacerbations in the previous year and since previous visit, smoking behaviour, BMI and comorbidity. Additional file 2 shows all items of the integrated health status. Questionnaires will be sent to patients’ homes at 0, 3, 6, 9, 12, 15 and 18 months (see Table 1).

**Table 1 T1:** Measuring moments

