#### ***Control group***

Patients in the control group will receive care as usual. The patients will visit their healthcare provider for the baseline measurement (0 months) and the 18-month follow up. At these consultations lung function and BMI will be measured, and smoking status, comorbidity, number of exacerbations in the previous year and since previous visit will be monitored. Questionnaires will be sent to patients’ homes at 0, 3, 6, 9, 12, 15 and 18 months (see Table 1).

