#### ***Secondary outcomes***

1. The net proportion of patients in the intervention group with a clinically meaningful change of 4 points on the SGRQ between baseline and 18 month follow-up [19], compared with the control group. The net proportion will be calculated by subtracting the percentage of patients improved by 4 points on the SGRQ from the percentage of patients decreased by 4 points.

2. The difference in the proportion of patients from the intervention group and control group with a clinically meaningful improvement of at least 4 points on the SGRQ (a decrease in the SGRQ score), between baseline and 6 months and between baseline and 12 months follow-up.

3. The absolute difference SGRQ score at 18-month follow-up between the intervention group and control group.

4. Health related quality of life will also be measured by the COPD Assessment Test (CAT) [20]. Differences on total scores will be calculated between baseline and 12 months follow-up and between baseline and 18 months follow-up. The CAT is an eight item questionnaire with scores ranging from 0 to 40, with higher scores indicating greater impairment of health related quality of life [20].

Differences in number of exacerbations and lung function, as recorded by the healthcare providers, will be calculated between the two groups, with respect to the number of exacerbations at a given time point and to change over time.

5. An economic evaluation will be performed at 6 and 12 months. This evaluation will compare differences in costs with differences in effects (Cost Effectiveness Analysis) and quality adjusted life years (Cost Utility Analysis).

Questionnaires will be used to record visits to physicians and healthcare providers, medication use, hospital admissions, employment status and absence from paid work every three months. For the economic evaluation, costs will be calculated from a healthcare perspective and a societal perspective.

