### Statistical analysis

All baseline variables and outcomes will be summarized with descriptive tables and, in the case of repeated measures, plotted against time per treatment arm.

The primary and first two secondary outcomes are binary outcomes and will be analysed with mixed logistic regression, using PQL2 or numerical integration as method of estimation.

All quantitative outcomes will be analysed with mixed linear regression, with physician, patient and measurement as three levels at which sampling error occurs, and as predictors treatment arm, time point of measurement, treatment by time interaction, patient demographics and other prognostic variables. Generalized linear mixed models with negative binomial distribution will be used to estimate the adjusted difference in exacerbations. Costs will also be analysed with generalized linear mixed models using a log-normal distribution or gamma distribution. A p-value of < .05 will be considered statistically significant.

All data will be analysed according to the intention-to-treat principle, including all randomised healthcare providers and patients. To prevent missing data, patients will receive reminders for the questionnaires if they do not return the questionnaire within three weeks. If necessary, multiple imputation to cope with missing values will be used [31].

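### Provider-recorded exacerbations are counted at four or more visits in the intervention arm but only at months 0 and 18 in control, so the between-arm comparison should be tied to the previous-year count at month 18

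*Protocol article*

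**What the plan says.** **Intervention arm** (Measurements, Intervention group): "Patients will visit their healthcare providers at least four times during the 18 months follow-up". At these consultations "healthcare providers will record lung function, number of exacerbations in the previous year and since previous visit". Table 1 schedules the ABC scale and the other clinic items, which only this arm completes, at months 0, 6, 12 and 18.

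**Control arm** (Measurements, Control group): "The patients will visit their healthcare provider for the baseline measurement (0 months) and the 18-month follow up". At those two visits "number of exacerbations in the previous year and since previous visit will be monitored". The earlier Control group section adds that the research team gives control providers no instruction.

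**Outcome** (Secondary outcomes): "Differences in number of exacerbations and lung function, as recorded by the healthcare providers, will be calculated between the two groups". The same sentence goes on to ask for the comparison both at single times and along the time course.

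**Analysis** (Statistical analysis): "Generalized linear mixed models with negative binomial distribution will be used to estimate the adjusted difference in exacerbations". Neither of these two sections says which of the two recorded items, previous year or since the last visit, enters the model.

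**A source with equal timing**: for the economic evaluation, "Questionnaires will be used to record visits to physicians and healthcare providers, medication use, hospital admissions", together with work items, every three months. Table 1 gives these questionnaires the same seven time points in both arms.

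**The concern.** A comparison of event counts is fair only if events are looked for in the same way in both arms. Here the number of post-baseline recordings, and for one of the two items the length of the look-back, depend on the allocated arm.

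- An exposure offset in the negative binomial model can correct for a longer or shorter window. It cannot correct for events being captured less completely in one long window than in several short ones, because completeness would then be confounded with treatment.
- At months 6 and 12 there is no control provider record. A between-arm comparison at those times, or a time course through them, has provider data from one arm only.

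Number of exacerbations is one of the secondary outcomes named in the abstract. If control events were under-counted, a tool that reduces exacerbations could look neutral or harmful on that outcome.

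**Working it through.** The protocol gives no figure for exacerbation rate, dispersion or completeness of recording, so there is no stated figure to reproduce. The first two steps use the text only. The last two are illustrations on assumed inputs.

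**1. Windows, from the text**

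| Item | Intervention (visits 0, 6, 12, 18) | Control (visits 0, 18) |
|---|---|---|
| Since last visit, after baseline | about 6 + 6 + 6 months | 18 months if the last visit is baseline; undefined if it is a usual-care visit |
| Previous year, at month 18 | months 6 to 18 | months 6 to 18 |
| Previous year, at month 0 | 12 months before baseline | 12 months before baseline |
| Provider record at months 6 and 12 | yes | none |

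Only the previous-year item at months 0 and 18 has the same window in both arms. It covers 12/18 = 67% of follow-up. The interim previous-year records in the intervention arm would not help even with a control counterpart: the month-6 record reaches back 6 months before baseline, and the month-12 and month-18 records overlap by 6 months.

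**2. Number of records.** With 180 patients per arm and the 25% dropout in Sample size calculation, 180 × 0.75 = 135 patients per arm complete. Post-baseline provider records are then at least 3 × 135 = 405 in the intervention arm and 1 × 135 = 135 in control.

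**3. Possible bias if the unmatched data are used.** Let c be control completeness relative to the intervention arm (assumed). The apparent rate ratio, intervention over control, is the true ratio divided by c.

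| c | True 1.00 appears as | True 0.80 appears as |
|---|---|---|
| 1.0 | 1.00 | 0.80 |
| 0.9 | 1.11 | 0.89 |
| 0.8 | 1.25 | 1.00 |
| 0.7 | 1.43 | 1.14 |

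A different assumption points the same way. Suppose the chance of capturing an event decays exponentially with its age. The captured share of a window of w months is then (1 − e^(−kw))/(kw), with k = ln 2 / half-life. Half-lives of 12, 24 and 48 months give 85%, 92% and 96% for a 6-month window, and 62%, 78% and 88% for an 18-month window. With no true effect the apparent ratios are 1.36, 1.18 and 1.09.

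For the effect on the test, assume 1 exacerbation per patient-year, dispersion 1 and the protocol's design effect of 1.38, which was derived for the binary SGRQ outcome. The standard error of the log ratio is √{1.38 × [(1/m1 + 1)/135 + (1/m2 + 1)/135]}, where m1 = 1.5 × true ratio and m2 = 1.5 × c. With a true ratio of 1.00 and c = 1.0, 0.9, 0.8, 0.7, the standard errors are 0.185, 0.187, 0.189 and 0.192. The chance of finding significantly more exacerbations with the tool is 2.5%, 8%, 22% and 46%. Power for a true 0.80 is only 22% even at c = 1.0, so the comparison is weak in any case.

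**4. Price of the matched window.** Without clustering and with dispersion 1, the ratio of standard errors for 12 versus 18 months is √[(1/m12 + 1)/(1/m18 + 1)], where m12 and m18 are the mean counts over 12 and 18 months:

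- 0.5 per year: √[(1/0.5 + 1)/(1/0.75 + 1)] = √(3.000/2.333) = 1.134
- 1.0 per year: √[(1/1.0 + 1)/(1/1.5 + 1)] = √(2.000/1.667) = 1.095
- 1.5 per year: √[(1/1.5 + 1)/(1/2.25 + 1)] = √(1.667/1.444) = 1.074

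**The case against.** The strongest reply is that a matched measure is already collected. Both arms record previous-year exacerbations at months 0 and 18, and the outcome wording can be met by the month-18 count and its change from baseline. Nothing commits the trial to the since-last-visit item or to between-arm comparisons at months 6 and 12, and a condensed article may leave the choice of variable to an analysis plan. This stands in part. It limits the point to a conditional one, but it does not remove it. The unequal schedule is fixed in the protocol itself, the outcome is worded to include change over time on provider records, and no later plan can create control records at months 6 and 12.

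Second, events are defined under Inclusion and exclusion criteria by prednisolone and/or hospital admission, which can be checked in records. Nothing says that counts rest on memory. This stands: capture may be close to complete in both arms, and the bias would then vanish. The protocol does not, however, require such a check.

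Third, fewer control visits belong to a comparison with usual care, and adding study visits would change that care. This is also right, and no extra visits are needed.

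A reader might infer that the planned model cannot separate a treatment effect from a recording effect at all. The documents do not support that. It would be true only of the unmatched data; the same model applied to the month-18 previous-year count has equal windows.

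**Conclusion.** The point holds in a limited form. Recording of exacerbations differs by arm in number, and for the since-last-visit item also in window. If the comparison uses that item or the interim provider records, differential ascertainment could bias it. The likely direction is against the intervention, because the arm questioned more often would tend to have more events recorded.

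The size cannot be established from the protocol. It ranges from nothing, if records capture all events, to an apparent ratio of 1.43 under no effect if control completeness is 70% of that in the intervention arm. All figures for bias, false-positive chance and power rest on assumed completeness, event rate and dispersion; those for the test also borrow a design effect from another outcome. They show what could happen and are not estimates for this trial.

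It would be wrong to infer that the trial's main conclusion is at risk. The SGRQ is sent to patients' homes on the same schedule in both arms, so the primary outcome is untouched. The point concerns one secondary outcome and is worth correcting because the remedy uses data already planned.

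**What to change.** Add one sentence each to Secondary outcomes and Statistical analysis:

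- **Main comparison.** Define the between-arm exacerbation outcome as the previous-year count recorded at month 18 in both arms. Analyse it with the planned negative binomial mixed model, adjusted for the baseline previous-year count and provider type, with a random effect for provider.
- **Data not used for between-arm inference.** Keep the month-6 and month-12 provider records and the since-last-visit item for describing the intervention arm only.
- **Supporting analysis over months 0 to 18.** Use hospital admissions from the three-monthly questionnaires, and prednisolone courses if the medication-use questions capture them. The article says only that medication use is asked, so this needs checking against the questionnaire.

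This needs no new visits, patients or questionnaires, and the primary analysis is unchanged. There are three costs. The main count covers 12 of 18 months, with a standard error about 7% to 13% larger at assumed rates of 1.5 to 0.5 per year. The supporting count rests on patient report. Some difference in awareness may remain, because intervention providers will also have seen their patients at months 6 and 12.
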